## Trial design

The study is a three-arm clustered parallel assignment, quasi-randomized, controlled trial (RCT) comparing INSETT+TRT and PIER to the wait list control group. The cluster is designed by the school. The schools were allocated into intervention groups or a control group using quasi-randomized design: The voluntary schools were first grouped based on whether they offered an introductory class or not. The TRT is targeted at recently arrived youth with a refugee background, and the PIER is targeted at mixed classes. The schools in the two groups were then randomly allocated to either intervention or control conditions using a random number generator [44]. The allocation aimed at equal numbers of schools in each condition. Due to the low participation rate, recruitment of schools was continued, which resulted in three additional schools all with introductory classes. The three additional schools were thus randomized either into the INSETT+TRT or control group. Blinding of participants, intervention providers, outcome assessors, or data analysts was not possible due to the explicit nature of interventions and a low number of project members. The decisions of data collection, recruitment, and training are discussed with other partners in the RefugeesWellSchool consortium but allowing each country to adopt the processes in the national framework. The control schools will receive the INSETT intervention toolkit after the research part of the project has ended. The trial aims to follow SPIRIT guidelines in reporting. Table 1 presents the SPIRIT figure, and the checklist can be found as an attachment.

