**Methods:**

A three-arm cluster RCT with parallel assignment, with a 1:1:1 allocation ratio, is applied in 16 schools that agreed to participate in the Refugees Well School interventions and effectiveness study. Schools were randomized to three conditions of two active interventions and a waiting list control condition. Students, their parents, and teachers in intervention and control schools participated in the study at baseline before the interventions, after the interventions, and at 6 to 12 months after the interventions. The primary effectiveness criterion variables are psychological distress (SDQ) symptoms, resilience (CYRM-12), and prosocial behavior (SDQ).

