## Study setting and participants

Power calculations were conducted before the data collection started. With alpha set at 0.05, power at 0.80, and rho = 0.05 (the intra-cluster correlation), a sample size of at least 40 clusters (i.e., schools) with 25 youths each was identified as necessary. Therefore, 500 youths per study arm (i.e., intervention or wait list control) were needed, resulting in 1500 total participants. To account for an expected drop-out rate of 20%, 1800 youths would have been recruited in total. To facilitate the recruitment of so many participants, recruitment was split between the Finnish study team and our team partners in Sweden.

The interventions were implemented in lower secondary schools with grades 7–9 and/or introduction classes for newcomer youth. We focused on immigrant youth who have resided in Finland for less than 6 years. Figure 1 presents the flowchart of the recruitment. Seventeen schools expressed their interest in participating in the study, but after allocation, one school dropped out. According to the randomization, eight schools were allocated into the INSETT+TRT intervention, three schools were allocated into PIER, and five schools served as waiting list controls. Also, Fig. 1 reports the numbers of students, teachers, and parents who answered the survey in the first round of data collection.

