In the core model (Fig. 2), there are two latent state variables, measuring true scores of PRE- and POST-intervention levels of the outcomes. The PRE-intervention state is indicated by the measured T1 variable without time-related measurement error because there is only one measurement point. In the case of POST-intervention state, there are two indicators, enabling the modeling of measurement error. The loadings of the indicators in the measurement part of the model are fixed to 1’s, meaning that the trajectory from T1 to T3 has the same shape for every individual. Only the level of PRE-intervention state and the difference between PRE- and POST-intervention states are random so that the means and variances of these variables within and between the clusters can be estimated. As predictors of the POST-intervention state, our model specifies the PRE-intervention state (path coefficient *a*, which is anticipated to be negative due to floor and ceiling effects), a dummy for intervention/control group membership (direct effect *c*), and potential mediating variables (path coefficient *e*, implying indirect effect *d*e* for intervention-control-group difference). The covariance between the PRE-intervention state and the dummy for intervention/control group membership (parameter *b*) is supposed to be 0, indicating that the randomization was successful. Moderation mechanisms are investigated by estimating the model simultaneously in groups created according to categorized moderator variables (multi-group SEM). Finally, the simple estimates of total intervention effects are calculated from a model without mediators and moderators (parameter *c* divided by the variance of POST-intervention latent variable, giving an equivalent to Cohen’s *d*).

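### The effect model compares each arm with pooled waiting-list controls and has no term for the school-type grouping within which schools were randomised

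*Protocol article*

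**What the plan says.** Trial design describes the allocation in steps. "The voluntary schools were first grouped based on whether they offered an introductory class or not". The reason given is that "The TRT is targeted at recently arrived youth with a refugee background, and the PIER is targeted at mixed classes". Then: "The schools in the two groups were then randomly allocated to either intervention or control conditions using a random number generator". Three schools recruited later all had introductory classes, and "The three additional schools were thus randomized either into the INSETT+TRT or control group".

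Study setting and participants gives the result: "eight schools were allocated into the INSETT+TRT intervention, three schools were allocated into PIER, and five schools served as waiting list controls". The abstract describes a three-arm cluster RCT "with a 1:1:1 allocation ratio". Trial design calls the design quasi-randomised and says that equal numbers of schools per condition were the aim.

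Under Analytic strategy, the legend to Fig. 2 codes intervention status as one waiting-list control category, INSETT+TRT and PIER. The text below it names three kinds of predictor of the post-intervention state: the pre-intervention state, the group dummy and potential mediators. Total effects come from the model without mediators and moderators. The covariance between the pre-intervention state and the dummy (parameter b) "is supposed to be 0, indicating that the randomization was successful".

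**The concern.** Randomisation within school type makes an arm comparable with the controls of its own type. It does not make that arm comparable with controls of the other type. If the five control schools are a mix, a pooled control group sets each active arm partly against schools that could not have been allocated to it.

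The pre-intervention state in the model removes only the part of a school-type difference that the baseline score carries. Schools with newcomer classes and other schools may also differ in how scores move over a school year. Such a difference would be reported as an intervention effect, with opposite signs in the two arms. Sociodemographic variables do not help, because they are listed only as possible moderators and the total-effect model leaves moderators out.

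The reading of parameter b has the same flaw. Balance is expected within school type, so b against pooled controls can differ from zero although the allocation was sound.

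**Working it through.** **The plan's own figure.** The only stated calculation is 500 youths per arm, with alpha 0.05, power 0.80, intra-cluster correlation 0.05 and 25 youths per school. No effect size is given, so the figure cannot be reproduced, only solved backwards. The design effect is 1 + (25 − 1) × 0.05 = 2.2, and the effective size per arm is 500/2.2 = 227. The implied difference is (1.96 + 0.84) × √(2/227) ≈ 0.26 SD two-sided, or 0.23 SD one-sided. It serves here only as a yardstick.

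**Which arm was open to which school.** The late schools could receive INSETT+TRT or control. The text presents this as following from their having introductory classes, so school type decided the available active arm. With PIER aimed at mixed classes, the natural inference is that the other group could receive PIER or control. If both groups were randomised to intervention or control, controls came from both, so 1 ≤ k ≤ 4.

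**Bias of the pooled contrast.** Let Δ be the difference in baseline-adjusted outcome, introductory-class schools minus the others, in the absence of any intervention. Relative to the schools without an introductory class, the pooled control mean is shifted by (k/5)Δ, the INSETT+TRT schools by Δ and the PIER schools by 0. Hence:

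- INSETT+TRT minus control: bias = Δ − (k/5)Δ = (1 − k/5)Δ
- PIER minus control: bias = 0 − (k/5)Δ = −(k/5)Δ

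The absolute biases add up to |Δ| for every k, so unless Δ is zero no split of the controls leaves both contrasts clean.

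**Size under an assumed Δ.** The table takes Δ = 0.3 SD (assumed). Type I error is for a two-sample t test on simulated school means (50,000 runs; 8, 3 and 5 schools, 25 students each, intra-cluster correlation 0.05). Each cell gives INSETT+TRT / PIER.

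| k | Bias in SD | Pooled type I error | Detectable difference with school-type term, SD |
|---|---|---|---|
| 1 | 0.24 / −0.06 | 0.232 / 0.044 | 0.88 / 0.63 |
| 2 | 0.18 / −0.12 | 0.139 / 0.056 | 0.66 / 0.68 |
| 3 | 0.12 / −0.18 | 0.085 / 0.082 | 0.56 / 0.76 |
| 4 | 0.06 / −0.24 | 0.055 / 0.131 | 0.51 / 0.96 |

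At Δ = 0.2 SD the absolute biases run from 0.04 to 0.16 SD. At Δ = 0 the pooled test holds its level at about 0.05. With a school-type term the simulated type I error was 0.048 to 0.052 for both contrasts, for every k from 1 to 4 and every Δ tried (0 to 0.5 SD).

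**Precision.** The standard deviation of a school mean is √(2.2/25) = 0.297 SD. The 80%-power detectable difference (normal approximation) is 2.80 × 0.297 × √(1/n₁ + 1/n₂). With pooled controls this is 0.47 SD for INSETT+TRT (8 v 5 schools) and 0.61 SD for PIER (3 v 5). With own-type controls only, the 5 becomes k for INSETT+TRT and 5 − k for PIER, which gives the last column of the table.

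**The case against.** The strongest reply is that much of this is inferred. The text never says outright that PIER was closed to schools with introductory classes, nor how the five controls divide. That stands, and the point is worded accordingly.

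Second, school type is not student type. Native-Finnish and refugee-immigrant students are included in both interventions. The 134 classes in 16 schools average 134/16 ≈ 8.4 per school, so schools with an introductory class may also contribute ordinary classes. With baseline adjustment already in the model, Δ may be small. This also stands: it limits the likely size but does not justify leaving out a factor used in the allocation.

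Third, a full covariate list is commonly left to an analysis plan. Here, however, the article itself lists the predictors and defines the total-effect model by what it excludes, so the stated model is open to comment.

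Four stronger readings are tempting but unsupported:

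- That b is fixed at zero in the model. The wording reads as an expectation to inspect, and only its interpretation is at fault.
- That 8:3:5 contradicts 1:1:1. Equal numbers were a stated aim and the actual split is reported openly.
- That the trial claims a randomised comparison of INSETT+TRT with PIER. The objectives compare each arm with the waiting list.
- That the few schools per group are a further defect. The Discussion already admits low power, and a school-type term would not cure it.

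**Conclusion.** The concern holds in this form: the stated effect model ignores the grouping used for allocation, and each contrast is therefore exposed to bias from any school-type difference in baseline-adjusted change. The exposure follows from the allocation text, given the inference about PIER and about controls coming from both groups.

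The amount of bias does not follow from the text. A reader might infer that the trial's results are shown to be wrong by some fixed fraction of an SD, but k and Δ are not given and at Δ = 0 there is no bias. Under the assumed Δ of 0.3 SD, the larger of the two biases is 0.18 to 0.24 SD for k from 1 to 4. That is not negligible beside a planned difference of about 0.26 SD, itself solved backwards. The primary effect estimates are affected and the grouping is known for every school, so the model should be changed before the effects are reported.

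**What to change.** Add the randomisation group (introductory class yes or no) as a school-level fixed effect in every effect model, including the total-effect model, so that each arm is compared with controls of its own school type. Report how the control schools divide between the two types. If either type has no control school, say that the corresponding contrast has no randomised comparator.

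Use the late batch of three schools only in a sensitivity analysis. As a fixed effect in the main model it could remove those schools from the contrast altogether if all three went to the same arm.

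Do not present b = 0 against pooled controls as evidence that randomisation worked; look at baseline balance within school type. Describe the design as two within-group randomisations of intervention versus control, not as a simple 1:1:1 three-arm randomisation.

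The data cost is one covariate already held for each school and one between-school degree of freedom. The real cost is wider intervals for both contrasts, and most for whichever arm has fewest controls of its own type. The normal approximation used above is optimistic with so few schools. This loss should be stated alongside the power limitation already acknowledged in the Discussion.

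### The stated 1:1:1 allocation ratio describes neither the procedure nor the result: school type limited the open arms, three late schools could not enter PIER, and the final count is 8:3:5

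*Protocol article*

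**What the plan says.** The Methods part of the abstract says that the design, "with a 1:1:1 allocation ratio, is applied in 16 schools". The Trial design section of the protocol article calls the trial quasi-randomised and gives the steps:

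- "The voluntary schools were first grouped based on whether they offered an introductory class or not".
- "The schools in the two groups were then randomly allocated to either intervention or control conditions using a random number generator".
- "The allocation aimed at equal numbers of schools in each condition".
- Recruitment continued because participation was low. It brought in three more schools, all with introductory classes: "The three additional schools were thus randomized either into the INSETT+TRT or control group".

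The Study setting and participants section reports "Seventeen schools expressed their interest in participating in the study, but after allocation, one school dropped out". It then presents the following as the outcome of randomisation: "eight schools were allocated into the INSETT+TRT intervention, three schools were allocated into PIER, and five schools served as waiting list controls".

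The Analytic strategy section gives the core model. The post-intervention state is predicted by the pre-intervention state, a dummy for intervention or control membership, and possible mediators. The covariance between the pre-intervention state and that dummy (parameter *b*) is supposed to be zero, as a sign that randomisation succeeded. The model as described has no term for the introductory-class grouping or for the late batch.

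**The concern.** An allocation ratio tells the reader what chance each unit had of entering each arm. If school type decided which arms were open, a single three-way ratio does not describe the trial, and a comparison against one pooled control group is not fully a randomised comparison. Some control schools could never have been in PIER, so they are not randomised comparators for it.

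Two things are at stake. First, a reader of the abstract will take this for a simple three-way randomisation that happened to come out uneven. Second, the planned model treats zero baseline covariance with arm as the mark of a successful randomisation. Under group-restricted allocation that is expected only within a group.

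**Working it through.** **1. The stated ratio against the reported count.** The inputs are 16 schools and 1:1:1 (abstract), and 8, 3 and 5 (Study setting and participants).

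- Total: 8 + 3 + 5 = 16, which agrees with the abstract.
- Under 1:1:1: 16/3 = 5.33 per arm, at best 6:5:5.
- Reported shares: 8/16 = 50%, 3/16 = 18.75%, 5/16 = 31.25%.

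The count alone does not disprove 1:1:1 as a procedure. If 16 schools were drawn independently with probability 1/3 per arm, a gap of five or more between the largest and smallest arm has probability 0.34. The count does conflict with the stated aim of equal numbers.

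**2. The stated ratio against the procedure.** For the three late schools the open arms were INSETT+TRT and control, so P(PIER) = 0, where 1:1:1 requires 1/3. Chance cannot produce that. The sentence also presents the restriction as a consequence of the schools having introductory classes, so it appears to come from the grouping rather than from lateness.

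**3. The school that left.** 17 − 1 = 16 = 8 + 3 + 5. The school left after allocation, so 8:3:5 is the count of schools that stayed. The randomisation result has one more school in one arm. The arithmetic also fits the three late schools being among the 17, which is assumed below.

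**4. Can the late split be recovered?** First-batch count = final count + dropped school − late schools. Each cell gives the 14 first-batch schools as INSETT+TRT : PIER : control.

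| Late split (INSETT+TRT:control) | Dropped from PIER | Dropped from INSETT+TRT | Dropped from control |
|---|---|---|---|
| 3:0 | 5:4:5 | 6:3:5 | 5:3:6 |
| 2:1 | 6:4:4 | 7:3:4 | 6:3:5 |
| 1:2 | 7:4:3 | 8:3:3 | 7:3:4 |
| 0:3 | 8:4:2 | 9:3:2 | 8:3:3 |

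All twelve histories end at 8:3:5. The most even first batch is 5:4:5, but 6:4:4 is close behind, and with a control drop-out the 3:0 and 2:1 splits are equally uneven (a range of 3 each). The split cannot be recovered from the text.

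**5. What the grouping does to parameter *b*.** Assume the natural reading, that introductory-class schools could enter INSETT+TRT or control and the other schools PIER or control. Let c of the 5 control schools have introductory classes, and let δ be the difference in mean baseline outcome between the two school groups. Weighting schools equally, the expected baseline differences are:

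- INSETT+TRT minus control: (1 − c/5)δ
- PIER minus control: (0 − c/5)δ

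These differ by exactly δ. For example, c = 2 gives 0.6δ and −0.4δ. Unless δ = 0, *b* cannot be zero for both intervention dummies, even if the randomisation was carried out perfectly. The documents give neither c nor δ.

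**The case against.** The strongest defence is that the authors disclose most of this themselves. The Trial design section calls the design quasi-randomised and describes both the grouping and the two-arm draw for the late schools, and the count of 8:3:5 is printed. On that view the error is one phrase in the abstract. This stands as to openness. It does not make 1:1:1 correct, and it does not alter the model, which as described takes no account of the grouping.

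A second objection is that the late batch need not bias INSETT+TRT versus control. If those schools were drawn with the same chances as the first-batch schools of their group, batch is balanced by design and any uneven split is chance. That is fair. It makes batch a stratum to include, not a reason to remove schools.

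A reader might go further and infer that all three late schools went to INSETT+TRT without a concurrent control, and that PIER lost one of four schools. The documents do not support this.

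- The inference treats an aim of equal numbers as if it had been achieved in the first batch. Under independent 1:1 draws a 3:0 split towards INSETT+TRT has probability 1/8, against 3/8 for 2:1 in the same direction.
- Recruitment closed in August 2019 and baseline ran from August to September 2019. No separate calendar is given for the late schools.
- The Recruitment and sampling section does not tie the three schools to the wave near asylum centres, and its first wave already included about 100 phone calls.
- The flowchart is not shown here and may give both the split and the arm of the school that left. Their absence from the text is therefore not counted as an omission.

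**Conclusion.** The point holds in limited form. The 1:1:1 ratio is wrong as written: it does not match the procedure (three schools with no chance of PIER, and allocation within groups defined by school type) or the result (8:3:5). The 8:3:5 count is also not the full randomisation result, because one of the 17 allocated schools is missing from it.

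The consequence for the analysis is that allocation group is tied to arm, and the core model as described neither includes the group nor allows for it when it supposes *b* to be zero. The size of any bias cannot be computed, because the number of schools per group and their baseline difference are not given.

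The conclusion about the late schools and PIER rests on the text alone. The algebra on *b* rests on reading the grouping as fixing the open arms for first-batch schools too. Nothing here shows a one-sided late batch or a lack of concurrent controls.

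**What to change.** 1. In the abstract, replace 1:1:1 with the allocation actually used: by introductory-class group and by batch, for all 17 schools, with the arm of the school that left.
2. In Study setting and participants, present 8:3:5 as the schools remaining after one withdrawal, not as the randomisation result.
3. In the core model, include allocation group as a school-level stratum and, for INSETT+TRT versus control, the late batch. State that *b* is expected to be zero only within allocation group.
4. Base the PIER contrast on schools that could have been allocated to PIER, at least as a sensitivity analysis.

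The team already holds these facts, so the cost is wording, one or two school-level indicators and one further analysis. The statistical price is real. An intercept and two arm dummies leave 16 − 3 = 13 school-level degrees of freedom, and two more terms leave 16 − 5 = 11. The PIER contrast, with only three PIER schools, may also lose some of its five control schools.

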**Table 1 Tab1:**
[figure not shown]
Study period for implementing interventions, collecting data (T1, T2, T3), and specific measures for adolescents, teachers, and parents

## Study setting and participants

Power calculations were conducted before the data collection started. With alpha set at 0.05, power at 0.80, and rho = 0.05 (the intra-cluster correlation), a sample size of at least 40 clusters (i.e., schools) with 25 youths each was identified as necessary. Therefore, 500 youths per study arm (i.e., intervention or wait list control) were needed, resulting in 1500 total participants. To account for an expected drop-out rate of 20%, 1800 youths would have been recruited in total. To facilitate the recruitment of so many participants, recruitment was split between the Finnish study team and our team partners in Sweden.

The interventions were implemented in lower secondary schools with grades 7–9 and/or introduction classes for newcomer youth. We focused on immigrant youth who have resided in Finland for less than 6 years. Figure 1 presents the flowchart of the recruitment. Seventeen schools expressed their interest in participating in the study, but after allocation, one school dropped out. According to the randomization, eight schools were allocated into the INSETT+TRT intervention, three schools were allocated into PIER, and five schools served as waiting list controls. Also, Fig. 1 reports the numbers of students, teachers, and parents who answered the survey in the first round of data collection.

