## Discussion

Most psychosocial interventions are targeted at immigrant children generally or to those who suffer from PTSD or other symptoms. There is a lack of universal interventions embedded in classrooms with both immigrant and native peers together [9, 19, 38]. Professionals recommend combining both preventive universal psychosocial elements and targeted clinical therapies, tailored according to the needs of immigrant children [18, 20, 32]. The number of immigrant children with an increased risk for mental health problems is growing. To understand the extended effect of school-based interventions, we need to broaden the research to include also information about child-, school-, and family-related factors [32, 38]. Similarly, the knowledge of what works for whom, why, and where would be of great importance when tailoring effective treatment for immigrant children. In trauma research, the relevant questions are about the factors and processes (or mechanisms) that explain (statistically mediate) the impact of war trauma on children’s and adolescents’ mental health and who are most vulnerable to negative trauma impacts, and why [75]. Analogously, in intervention studies, it is critical to know what explains the potential change and to whom interventions work and why.

As a limitation to the study, unfortunately, the recruitment did not reach the needed number of clusters for adequate power of 80%. The problems in the recruitment may have been because many schools had other ongoing interventions or had just participated in similar training. Some schools with a long history of teaching immigrant students doubted the intervention could provide them with any new tools. In more rural schools near asylum centers, the number of immigrant students had decreased rapidly after the great influx in 2015, and the intervention was thus not seen as necessary anymore. The low power will limit our chances of finding statistically significant effects on a school level.

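### The sample-size figures disagree: 40 schools of 25 make 1000 pupils, but 500 per arm in three arms makes 1500 (60 schools), and 20% drop-out requires 1875 recruited, not 1800

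*Protocol article*

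**What the plan says.** All the sample-size figures stand in the first paragraph of Study setting and participants in the protocol article. The design inputs are given as "With alpha set at 0.05, power at 0.80, and rho = 0.05 (the intra-cluster correlation"; no effect size is stated, nor whether the test is one- or two-sided. From these inputs, "a sample size of at least 40 clusters (i.e., schools) with 25 youths each was identified as necessary". The next sentence concludes that "500 youths per study arm (i.e., intervention or wait list control) were needed, resulting in 1500 total participants". The drop-out allowance follows: "To account for an expected drop-out rate of 20%, 1800 youths would have been recruited in total". The paragraph ends by saying that recruitment was divided between the Finnish team and partners in Sweden, without giving either share.

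The next paragraph reports the Finnish allocation: "eight schools were allocated into the INSETT+TRT intervention, three schools were allocated into PIER, and five schools served as waiting list controls". The Abstract and Trial design describe a three-arm trial with the school as the cluster, and Analytic strategy says that the interventions are given at school level.

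The Discussion concedes that too few clusters were recruited for 80% power and adds: "The low power will limit our chances of finding statistically significant effects on a school level".

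**The concern.** The number of schools and the number of pupils cannot both describe the same three-arm trial. The text presents the 500 per arm as following from the 40 schools, but 40 schools of 25 fall 500 pupils short of 1500. In a cluster trial the number of clusters largely determines power, so the figure left unscaled is the more important one. A reader cannot tell whether the stated 80% belongs to one comparison of two arms with 40 schools or to the whole trial.

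Two smaller faults sit beside this. The drop-out allowance multiplies by 1.2 where it should divide by 0.8. And the Discussion's phrase about effects at school level could be taken to mean that pupil-reported outcomes escape the power problem. They do not: allocation is by school, so each contrast of an intervention with control is a between-school contrast.

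**Working it through.** **Inputs from the protocol article.** Alpha 0.05, power 0.80, ICC 0.05, 40 schools, 25 pupils per school, 500 per arm, 1500 in total, 20% drop-out, 1800 recruited, and 8, 3 and 5 Finnish schools allocated to INSETT+TRT, PIER and control.

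**Assumptions, because the article does not give them.** A two-sided test; a standardised difference d; equal school sizes; 25 to 100 pupils per school for the schools actually allocated (the counts are in a figure that is not reproduced in the text at hand); no baseline adjustment; and no allowance for the grouping of schools by whether they offer an introductory class.

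**1. Reproducing the printed figures.** One route gives all of them:
- 40 schools / 2 arms = 20 schools per arm
- 20 × 25 = 500 pupils per arm
- 500 × 3 arms = 1500
- 1500 × 1.2 = 1800

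So 40 works as the count for one two-arm comparison. Spread over three arms it does not: 40 × 25 = 1000, and 1000/3 = 333 per arm, not 500.

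**2. Schools needed for the printed pupil numbers.** 1500/25 = 60 schools, or 500/25 = 20 per arm.

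**3. Drop-out.** 1800 × 0.8 = 1440 (480 per arm), which is 60 below 1500. The number to recruit is 1500/(1 − 0.20) = 1875 (625 per arm), which is 75 more than 1800.

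**4. Effect size implied by 20 v 20 schools.** Design effect = 1 + (25 − 1) × 0.05 = 2.2.
- Normal approximation: d = (1.96 + 0.84) × √(2 × 2.2/500) = 0.263.
- t-test on school means, each with variance ICC + (1 − ICC)/m = 0.05 + 0.95/25 = 0.088 and 38 degrees of freedom: d = 0.27.
- A one-sided test would give 0.23 by the normal approximation.

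**5. What the school count does to power.** With 40 schools over three arms there are 13.3 per arm. At the back-solved effect, power is 62% by the t-test (63% by the normal approximation) instead of 80%. Over a wider assumed range (normal approximation), going from 20 to 13.3 schools per arm lowers power from 57% to 41% at d = 0.20 and from 99% to 94% at d = 0.40.

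**6. What the drop-out slip does to power.** With 480 analysed per arm (24 in each of 20 schools), power at the back-solved effect is about 79%, a loss of about 1 point.

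**7. The schools actually allocated.** t-test on school means, ICC 0.05, unadjusted:

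| Pupils per school (assumed) | Variance of a school mean | Detectable d at 80% power, 8 v 5 (INSETT+TRT v control) | Detectable d at 80% power, 3 v 5 (PIER v control) |
|---|---|---|---|
| 25 | 0.088 | 0.52 | 0.73 |
| 50 | 0.069 | 0.46 | 0.65 |
| 100 | 0.0595 | 0.43 | 0.60 |

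Four times as many pupils per school lowers the detectable difference by less than a fifth; the number of schools sets the limit.

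**The case against.** The gloss on what a study arm means, intervention or wait list control, points to a two-group calculation. On that reading 500 per arm and 1500 in total follow exactly, and the fault is a school count without a label. This stands: the pupil target of 1500 is not shown to be wrong, and the 62% applies only if 40 schools really were meant to cover three arms. But the text never says that 40 is for one comparison and never gives 60, so the printed figures still disagree.

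A reader might infer that the article misreports its shortfall, as 16 of 40 schools when it is 16 of 60. The documents do not support this. The Discussion publishes no fraction, and its statement that too few clusters were recruited is true against 40 or 60. Nor is 60 shown to be the denominator for the 16 Finnish schools, since the target was shared with Sweden and no Finnish share is given.

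A reader might also take the Discussion to confine the power problem to school-level effects only. It does not say only, and because the interventions are given at school level the phrase can fairly be read as meaning the intervention effects. It is unclear rather than wrong.

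The detectable effects in the table are unadjusted, whereas the planned model regresses the post-intervention state on the pre-intervention state and uses two post-intervention measurements. With an assumed baseline correlation of 0.5 to 0.7 at both levels, they shrink by a factor √(1 − r²) of 0.87 to 0.71; 0.52 would become about 0.45 to 0.37. This stands, and the table should be read as the unadjusted case.

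Finally, school recruitment closed in August 2019 and the low power is openly declared, so no allocation or analysis changes. That bears on the cost of the correction, not on whether the figures agree.

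**Conclusion.** The sample-size statement is wrong as written. Forty schools of 25 do not make 1500 pupils; three arms of 500 need 60 schools. The likeliest explanation is a two-arm school count left unscaled when the pupils were tripled. The drop-out figure should be 1875, a small error in its effect on power. These results are plain arithmetic on the article's own numbers and need no assumption.

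The size of the consequence does rest on assumptions. The drop from 80% to about 62% uses a back-solved d of 0.26 to 0.27, which is not a design value that the authors stated. The detectable effects of about 0.52 to 0.43 (8 v 5 schools) and 0.73 to 0.60 (3 v 5) further assume 25 to 100 pupils per school and no baseline adjustment. They support the conclusion that both contrasts will be imprecise, PIER v control the more so. They do not support the stronger inference that a null result would carry no usable evidence: an estimate with its confidence interval would still be informative, and the planned adjustment should narrow it.

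**What to change.** Under Study setting and participants:
- say that 40 schools is the requirement for one comparison of two arms, and that three arms need 60 (20 per arm) across Finland and Sweden together;
- change 1800 to 1875;
- have the authors state the effect size they used. The back-solved value should not be written in as if it had been the design assumption.

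In the Discussion, replace the sentence on low power with one saying that every intervention-v-control contrast is affected because schools were allocated. Give the detectable effect for the 8 v 5 and 3 v 5 school contrasts with its assumptions: ICC, actual pupils per school, and whether baseline is adjusted for.

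The cost is a few sentences and one short calculation with the actual school sizes. No further schools, data or changes to the analysis are needed.
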